### Sample size

PROSPECTOR-1: A total of 120 participants are planned for inclusion (60 per arm). This sample size was chosen to provide a precise estimate of feasibility outcomes with a width of CI being <20% for any proportion. Such a sample size would also likely provide a reliable estimate of effectiveness as it has been shown that with binary outcomes, gain in precision is smaller once each group reaches 60 participants.^38^ This sample size also likely represents >9% of the definitive trial’s sample size (to detect a 5% difference assuming 8% event rate with 90% power and 5% significance level, a total of almost 900 participants would be required).^38^

PROSPECTOR-2: A total of 830 participants are planned for inclusion (415 per arm). The incidence of delayed reactions after single-dose oral challenge in the current literature is approximately 3%,^20^ while the incidence of delayed reactions after prolonged oral challenge is approximately 8%.^27 39^ To detect a 5% difference with 85% power and 5% significance level, 372 participants would need to be randomised to each arm. To account for a 10% loss to follow-up, a total of 830 participants will be recruited.

As the stipulated 5% difference reported in the literature and observed in our pilot data is not regarded as clinically relevant by many drug allergy specialists, we will also evaluate the non-inferiority of single-dose challenge. Given the lesser severity of an adverse event, a clinically relevant non-inferiority margin was determined to be 10% among investigators of this study. The planned sample size will enable us to evaluate a non-inferiority of the risk difference between study arms (secondary outcome) with double-sided 95% CI with 82% power (assuming real difference between arms being 5%).^40^ The sample size for PROSPECTOR-2 will be updated prior to study start based on the estimates observed in PROSPECTOR-1.

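### The 10-point non-inferiority margin is larger than the 8% reaction rate assumed for the prolonged arm, so meeting it would not show that single-dose challenge preserves any detection

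*Protocol article*

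**What the plan says.** All the planning figures are in the Protocol article, Sample size, PROSPECTOR-2.

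- Single-dose rate: "The incidence of delayed reactions after single-dose oral challenge in the current literature is approximately 3" per cent.
- Prolonged rate: "the incidence of delayed reactions after prolonged oral challenge is approximately 8" per cent.
- Superiority: "To detect a 5% difference with 85% power and 5% significance level, 372 participants would need to be randomised to each arm". After allowance for loss, "A total of 830 participants are planned for inclusion (415 per arm").
- Reason for adding non-inferiority: the 5-point difference "is not regarded as clinically relevant by many drug allergy specialists".
- Margin: "a clinically relevant non-inferiority margin was determined to be 10% among investigators of this study". The grounds given are the lesser severity of the event and the investigators' judgement.
- Non-inferiority precision: the risk difference is assessed "with double-sided 95% CI with 82% power (assuming real difference between arms being 5" points).

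Non-inferiority is labelled a secondary outcome. The text does not relate the margin to the 8% rate or to a proportion of reactions that single-dose challenge must still reveal.

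**The concern.** The endpoint is a positive challenge, so a lower rate in the single-dose arm means fewer reactions brought to light. A non-inferiority margin on that scale should mark the point at which too much detection has been lost. If the margin exceeds everything that the prolonged arm is expected to find, no loss can reach it, and a pass does not imply that any detection was kept.

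The non-inferiority power is also calculated at the 5-point difference on which the superiority test is sized. A trial that goes to plan would therefore tend to report both findings. The article's Background presents practice on this question as divided, and the word non-inferior in the report could be taken as evidence that single-dose challenge detects nearly as much.

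**Working it through.** **Inputs.** Rates of 8% and 3%, a margin of 10 points, a two-sided 95% CI, 372 per arm needed and 415 per arm recruited (all from Sample size). Alternative prolonged-challenge rates come from Background and rationale: 5.5% (European guideline review), 7.2% (Danish retrospective study, after day 1) and 5–12% (European studies). Assumption: unadjusted comparisons, without the planned adjustment for site and setting.

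**1. Reproduce the plan's figures.**

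- Superiority: n = [1.96·√(2·0.055·0.945) + 1.036·√(0.08·0.92 + 0.03·0.97)]² / 0.05² = 371.8, so 372 per arm, as stated. Then 372/0.9 = 413.3, so 414 per arm and 828 in total, against 830 stated.
- Non-inferiority power at 372 per arm: SE = √(0.1027/372) = 0.01662.
  - Simple normal formula: Φ((0.10 − 0.05)/0.01662 − 1.96) = Φ(1.049) = 85.3%.
  - With continuity correction 1/n: Φ((0.05 − 0.00269)/0.01662 − 1.96) = 81.3%.
  - Exact binomial enumeration: 80.8% with the Newcombe interval, 84.0% with Wald.

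  The stated 82% lies within this range and is not an error.

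**2. Compare the margin with the rate.** With a prolonged rate of 8%, the deficit is 8% minus the single-dose rate. Its maximum is 8 − 0 = 8 points, which is below 10. The null hypothesis of a deficit of 10 points or more cannot be true at the design rate.

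**3. How often would non-inferiority be declared with no single-dose reactions?** Exact binomial enumeration, declaring non-inferiority when the upper 95% limit is below 10 points:

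| Prolonged rate | 372 per arm (Newcombe–Wald) | 415 per arm (Newcombe–Wald) |
|---|---|---|
| 8% | 21–34% | 26–39% |
| 7.2% | 41–57% | 48–63% |
| 5.5% | 87–94% | 92–96% |

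For example, 27/372 (7.3%) against 0/372 has a Wald upper limit of 9.9 points and passes. An observed 30/372 (8.1%) against 0/372 has an upper limit of 10.8 points and fails. Under Newcombe the largest passing count is 25/372.

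**4. Joint result at 8% versus 3%.** The expected Wald interval at 372 per arm is 5 ± 1.96·1.66, that is 1.7 to 8.3 points, which lies above 0 and below 10. By enumeration (Newcombe–Wald):

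| Per arm | Prolonged superior | Single dose non-inferior | Both |
|---|---|---|---|
| 372 | 86–87% | 81–84% | 67–71% |
| 415 | 90% | 85–87% | 75–77% |

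**5. What a tighter margin costs.** As an illustration only, take a 4-point margin with no true difference and 8% in both arms. SE = √(2·0.08·0.92/372) = 0.01989, and power = Φ(0.04/0.01989 − 1.96) = Φ(0.051) = 52%. Enumeration gives 51–52% at 372 per arm and 55–57% at 415. Calculating this power at 3% in both arms gives 86–89% at 372, but a 4-point margin would then again exceed the whole rate.

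**The case against.** The strongest defence is that a difference above zero and a difference below 10 points are compatible statements about one confidence interval. The plan explains why it wants both: many specialists do not regard 5 points as clinically relevant. A result that is superior but within tolerance is therefore deliberate. That stands, and a reader who infers that the plan powers two contradictory claims goes too far. The rationale might support tolerating 5 points, but it does not explain a margin of twice that size that exceeds the whole assumed rate.

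A reader might also infer that the test cannot separate a good single-dose strategy from a useless one. The figures do not support this. At 372 per arm, non-inferiority is declared in 81–84% of trials at 8% versus 3% but in 21–34% at 8% versus 0%, where it usually fails. It becomes likely with zero detection only at lower prolonged rates.

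Three further limits stand. The Background cites European rates of up to 12%, which the margin does not exceed. Under Eligibility criteria, everyone randomised has tolerated a supervised first dose, so no detection here means no later reactions, not a challenge that finds nothing at all. Finally, the comparison is secondary, a rule for reading joint results may be in the analysis plan, and the sample size is to be updated from PROSPECTOR-1. None of this ties the 10-point margin to the rate it is applied to.

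**Conclusion.** The concern holds for the margin and its interpretation. At the plan's own 8% prolonged rate, every possible single-dose rate is truly within 10 points, including zero. A declaration of non-inferiority therefore does not show that single-dose challenge preserves any detection of delayed reactions. With zero single-dose reactions and 372 per arm, the chance of that declaration is 21–34% at 8% and rises to 87–94% at 5.5%. At the design rates, both findings together are the most likely outcome, at 67–71% (75–77% at 415 per arm).

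These figures rest on unadjusted binomial comparisons and on the planning rates. If the true prolonged rate were above 10%, the null hypothesis would become possible again. A reader might suspect the 82% power because the simple formula gives 85.3%, but other standard methods reproduce it. The primary superiority comparison and its sample size are sound on this point.

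**What to change.** Take one of two routes for this secondary outcome.

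1. Make no non-inferiority claim on the 10-point margin. Report the risk difference with its two-sided 95% CI and let readers judge it against the difference they would tolerate. This changes wording only and needs no extra participants.
2. Keep the claim with a margin below the assumed prolonged-arm rate, justified by the share of reactions that single-dose challenge must still detect. The investigators should choose it before unblinding and restate the power under the planned rates. The 4-point illustration, with 51–52% power at 372 per arm if both arms are at 8%, shows that a useful margin may not be well powered at the present size. The planned update from PROSPECTOR-1 is a natural time to settle this.

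State in advance how a joint result will be reported: prolonged challenge detects more, by an amount within the tolerated difference. The cost is a weaker or less well powered secondary claim. The primary analysis does not change.

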### Recruitment

Recruitment will be undertaken by appropriately trained and delegated study investigators at participating sites in both the ambulatory clinic and inpatient settings. The central study team will monitor and encourage recruitment by regularly engaging with participating site staff, providing strategies for boosting enrolment and troubleshooting solutions. Recruitment number updates will be communicated through a regular study newsletter.

### Consent

Eligible patients will be provided with a verbal explanation of the project by a delegated study investigator and a paper or electronic consent form to read through (online supplemental materials 1 and 2). They will be encouraged to ask questions and discuss their participation with family, friends or a trusted family doctor if helpful. A thorough assessment of the participant’s capacity to make a valid informed decision will be made by the study investigator before the patient is recruited and documented informed consent is obtained.

### Methods: assignment of interventions

#### Allocation

Permuted block design randomisation will be used, stratified by the hospital site and setting (inpatient vs outpatient). While block design might result in larger treatment imbalances, such design is preferred to overcome logistical difficulties. Randomisation will be performed by the unblinded pharmacy dispensing team via REDCap just before the intervention. The allocation sequence will be concealed until the time of the randomisation.

#### Blinding

Participants (and their caregivers if applicable) as well as study investigators and research staff will be blinded to the assigned intervention. Adverse Event Review Panel members will be blinded to the assigned intervention. Clinical trials pharmacists will be unblinded.

Participants may be unblinded during the 7-day follow-up period in the event of a serious adverse event (SAE) or grades 3 or 4 adverse event and if the site principal investigator deems this appropriate. If a participant’s assignment is revealed, the Sponsor and Coordinating Principal Investigator will be notified within 24 hours of unblinding. The date and reason for the blind broken must be recorded in the source documentation and case report form. All participants may be unblinded at the 90-day follow-up to allow for those in the control arm to receive a prolonged challenge if that is the site’s practice or preference.

### Methods: data collection, management and analysis

#### Data collection methods

De-identified clinical data will be stored in a secure electronic REDCap database, hosted by the University of Melbourne. Each participating centre will only have access to their own patient data. All electronic and paper data will be retained for a period of 15 years after which all data will be destroyed according to hospital policy in place at the time.

#### Progression from pilot to definitive trial

PROSPECTOR-2 will proceed immediately on completion of PROSPECTOR-1, provided the following criteria are met:

Compliance with study medication is ≥80%.Unblinding is ≤10%.Recruitment to eligibility ratio ≥80%.

If these criteria are not met, appropriate amendments to the study design of PROSPECTOR-2 will be made. If compliance is under 80%, additional reminders will be scheduled for participants. If unblinding exceeds 10%, the trial will be converted to open label. If the recruitment to eligibility ratio is lower than 80%, additional strategies for recruitment may be considered.

### Statistical methods

#### PROSPECTOR-1

The results will be presented according to CONSORT guidelines for feasibility studies.^41^ Patient characteristics and penicillin allergy history will be presented by arm using median (IQR) for continuous variables and count (percentage) for categorical variables. Binary outcomes will be presented as count and percentage with 95% exact CIs. All outcomes (where feasible) will be presented as overall, by study arm and by setting. Exploratory efficacy outcomes will also be presented as absolute (risk difference) and relative difference (risk ratio) with 95% CIs. No statistical tests will be performed. The amount and pattern of missing data will be explored.

#### PROSPECTOR 2

The results will be presented according to CONSORT guidelines.^42^ Patient characteristics and penicillin allergy history will be presented by arm using median (IQR) for continuous variables and count (percentage) for categorical variables. The primary analysis will be on an intention-to-treat basis. A generalised linear model with binomial family will be used to calculate the risk difference (identity link) and risk ratio (log link) between intervention and control. The results will be presented with two-sided 95% CIs. Models will be adjusted for stratification variables (clinical site and setting). Subgroup analysis will be performed by the inclusion of an interaction term between subgroup and arm. The primary analysis will also be performed in the per-protocol population. Time to adverse reaction will be evaluated using the Kaplan-Meier method and Cox proportional hazards regression. A detailed statistical analysis plan will be prepared and uploaded to the Australian New Zealand Clinical Trials Registry (ANZCTR) listing before study completion.

### Oversight and monitoring

#### Adverse event review panel

A blinded independent review panel consisting of an allergist and a dermatologist will be established to review reported adverse drug reactions for both PROSPECTOR studies. A summary of the patient’s reaction will be compiled, comprising a standardised symptom questionnaire and clinical photography of any rash, cutaneous or mucosal change. The review panel will provide a determination of whether the reported reaction is to be classified as an ‘immune-mediated adverse drug reaction’. This classification will be provided to the data safety monitoring board (DSMB) for further deliberation in addition to the stipulated reports.

#### Data safety monitoring board

A DSMB will be established to review trial data and monitor the progress of each trial. The DSMB will monitor adherence to the protocol, participant recruitment, outcomes and participant safety data. They will also monitor the assumptions underlying sample size calculations for the study and alert the investigators if an increased recruitment effort is required. The DSMB will make recommendations as to whether the study should continue or be terminated, consider participant safety or other circumstances as grounds for early termination, including either compelling internal or external evidence of treatment differences or feasibility of addressing the study hypotheses (eg, poor participant enrolment).

## Ethics and dissemination

These studies were reviewed and approved by the Austin Health Human Research Ethics Committee (Reference Numbers: PROSPECTOR-1: HREC/99740/Austin-2023 and PROSPECTOR-2: HREC/109785/Austin-2024). Additional approvals will be sought for international PROSPECTOR-2 sites before their participation in the study. The results will be published in peer-reviewed journals and presented at relevant conferences.

### Harms

Adverse events will be recorded from the time of randomisation until day 90. Patients will be supplied with a prescription for oral corticosteroids and second-generation antihistamines on hospital discharge, only to be used in the event of an immune-mediated positive oral challenge, as instructed by the site investigators at the time of the days 1, 5, 7 and 14 reviews. Participants will be instructed by site investigators to fill this script at their own expense if required.

### Patient and public involvement

No patient and/or public were involved in the study development.
